### Subgroups for analysis

A floor effect may affect the outcomes measured on participants who present with subclinical symptoms, for whom *substantial* change is not anticipated. In order to mitigate the potential dilution of significance incurred by a floor effect, sub-groups for analysis will be defined as:

Participants with total *t-*scores on the MASC-10 of > =56.Participants with total *t-*scores on the MASC-10 of <56.

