### Sample size

A difference of ±5 in the *t-*score on the primary outcome measure (MASC-10) after an 8-week period can be considered clinically significant (March,
1997). To achieve a power of 80% at a significance level of 5%, 63 participants per study arm are required, a total of 126 children from 14 schools. This calculation is based on a sample size requirement for an individually randomised trial of 64 participants per arm, adjusted by a design effect of 0.98, which accounts for clustering and adjustment for baseline values. A target sample of 154 participants will be recruited to allow for possible 10% attrition.

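### The MASC-10 split at 56 is set up to protect significance; separate subgroup tests are under-powered and cannot show that the effect varies with baseline severity

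*Protocol article*

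**What the plan says.** Under Subgroups for analysis, the protocol article states that "A floor effect may affect the outcomes measured on participants who present with subclinical symptoms", and that no large change is expected in these children. It continues: "In order to mitigate the potential dilution of significance incurred by a floor effect, sub-groups for analysis will be defined as" MASC-10 T-scores of 56 or more, and below 56.

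Under Participants, children are chosen on the judgement of school staff, and no MASC-10 threshold is set for entry. Under Sets for analysis, the Primary ITT set keeps all randomised participants, so low scorers stay in the primary comparison.

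Under Sample size, a 5-point T-score difference "on the primary outcome measure (MASC-10) after an 8-week period can be considered clinically significant". The section then states: "To achieve a power of 80% at a significance level of 5%, 63 participants per study arm are required". This comes from a "sample size requirement for an individually randomised trial of 64 participants per arm". The figure is then multiplied by 0.98, a single factor meant to cover both the clustering and the gain from baseline adjustment.

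Under Statistical analysis, the model has arm, repeated-measures factors and their interactions, with baseline score and school decile as covariates. There is one planned primary comparison. False discovery rate control applies to the secondary hypotheses. The section names no interaction of arm with baseline MASC-10, and it does not say whether subgroup tests belong to the false discovery rate family.

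**The concern.** Whether the programme works better in children who start with more anxiety is a fair question. The stated reason for the subgroups is different: to keep a floor effect from diluting significance. Read plainly, that means looking for a significant result in the part where one is thought more likely.

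A significant result at 56 or above beside a non-significant one below 56 is not evidence that the two effects differ. Each half-sample test has modest power, so such a pattern arises easily when the effects are equal. The likely harm is a claim that the intervention works only above 56 when the data cannot support it.

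There is also a gap between two sections. One anticipates children who respond little; the other sizes the trial on a single 5-point mean difference with no visible allowance for them.

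**Working it through.** **Inputs.** From Sample size: difference 5 points, power 80%, significance level 5% (taken as two-sided), 64 per arm individually randomised, design effect 0.98, "a total of 126 children from 14 schools". Not in the article: the SD, the share of children below 56, and the effect in those children.

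**Reproducing the plan's figure.** With SD 10, a two-sample t calculation gives 64 per arm (63 by the normal approximation). SD 9 gives 51 and SD 11 gives 76 by the normal approximation, so SD 10 is implied. Then 64 × 0.98 = 62.7, rounded up to 63 per arm, 126 in total. The calculation therefore uses an undiluted 5-point mean difference.

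**Baseline power.** Effective size per arm is 63 / 0.98 = 64.3. The noncentrality is 5 / (10 × √(2/64.3)) = 2.83. Power is 80% with 124 df.

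**Power of one half-sample test.** With an even split, the effective size per arm is 32.1. The standard error is 10 × √(2/32.1) = 2.49, and the noncentrality is 5 / 2.49 = 2.00. Power is about 51% (61 df; 52% by the normal approximation). This carries the 0.98 over to the subgroup, which is an assumption.

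**What separate tests show.** Let p = 0.52 be the power in each half when the true effect is 5 points in both. The chance that exactly one half is significant is 2 × 0.52 × 0.48 = 0.50. So about half the time the results look like effect modification where there is none. If there is no effect anywhere and both tests are run at 5% without adjustment, the chance of at least one significant result is 1 − 0.95² = 9.75%.

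**Power of the interaction.** For a 5-point difference between the effects in two equal halves, the standard error is √2 × 2.49 = 3.53. The ratio is 5 / 3.53 = 1.42, and power is Φ(1.42 − 1.96) = 29%. A continuous interaction will differ somewhat, depending on the spread of baseline scores.

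**Sensitivity of the primary power.** Let s be the share below 56 and e their effect, with 5 points in the others. The mean effect is 5(1 − s) + es, and power is computed as above with 124 df.

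| Share below 56 (assumed) | Effect there (assumed) | Mean effect | Power |
|---|---|---|---|
| 0% | – | 5.00 | 80% |
| 25% | 0 | 3.75 | 56% |
| 50% | 0 | 2.50 | 29% |
| 25% | 2 | 4.25 | 67% |
| 50% | 2 | 3.50 | 50% |

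For the mean to stay at 5 with no effect below 56, the others would need 5 / 0.75 = 6.7 points or 5 / 0.50 = 10 points. The article claims no such effect.

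**The case against.** The strongest reply is that the article only defines two subgroups. How their effects are estimated may be left to the full analysis plan, and the blind review is still to finalise that plan. This stands as far as it goes: the absence of an interaction term from a journal article would not be a finding by itself. What the article does fix is the cut-point and its purpose, and that purpose leads to within-subgroup testing.

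Four stronger readings are tempting, and the document does not support them.

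- A reader might infer that a subgroup result could stand in for the primary result. It cannot: the parallel ITT comparison is the one planned test of the primary hypothesis.
- A reader might infer that the subgroup tests have no multiplicity control. The article neither includes nor excludes them, so the 9.75% applies only if they are left unadjusted.
- A reader might infer that the sample size assumes 5 points in every child. It gives 5 points as a clinically significant difference to detect. A mean of 5 could hold if higher scorers gain more.
- A reader might infer that, on the plan's own expectation, the stated power is wrong. The floor effect is worded as a possibility, and little change is not zero change. The Background also reports that symptoms in control groups typically rose, so low scorers could still show a difference between arms.

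The size of any dilution is also open. Staff select for early anxiety symptoms, so few children may score below 56. With 20% below 56 and 2.5 points there, the mean effect is 4.5 and power about 72%.

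Finally, a pre-specified cut is not an error in itself, and the primary analysis keeps baseline as a covariate. The case for a continuous term is that it answers the question better at almost no cost.

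**Conclusion.** The point holds as a cheap improvement to a secondary analysis and does not undermine the primary test. A split at 56 justified by protecting significance leads to tests with about 51% power for 5 points in half the sample (SD 10, design effect 0.98, even split). Those tests cannot show that the effect differs by baseline severity. The article also leaves open whether they fall under false discovery rate control.

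The secondary point is that the sample size section makes no visible allowance for the low responders anticipated elsewhere. Against 80% undiluted, power is about 56% to 29% if 25% to 50% of children score below 56 with no effect, and about 67% to 50% if their effect is 2 points. These figures depend on an inferred SD and on assumed shares and effects. They show sensitivity and are not a forecast.

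**What to change.** - Replace the split with one treatment by continuous baseline MASC-10 interaction in the full Primary ITT model, using the post-intervention contrast for the primary outcome. Report the estimated treatment effect with its confidence interval at several baseline scores, including 56.
- If subgroups are still displayed, define them by the baseline score, label them exploratory, and say whether any tests on them enter the false discovery rate family.
- Drop protection of significance as the rationale, and state the aim as estimating how the effect varies with baseline severity.
- Add a short power sensitivity statement to the sample size section, over a range of shares below 56 and effects in those children, marked as assumption-based.

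The cost is wording and one model term, with no change to recruitment or data collection. There are two downsides. The interaction test has low power (about 29% for a 5-point difference between equal halves), so a non-significant interaction must not be read as evidence of a uniform effect; the emphasis belongs on the intervals. The stated power will also look less favourable.

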### Statistical analysis

A Repeated Measures Analysis of Covariance (RM-ANCOVA) analysis of the data will allow comparisons of between-subject (intervention versus waitlist control) and within-subject (repeated measures on outcomes) factors and their interactions, while statistically controlling for baseline scores, cluster’s decile rank and other potential covariates that may be identified as the result of the blind review (e.g. gender, individual’s score on screening instrument). Incorporating individual-level covariates is more efficient (statistically) than cluster-level covariates (Eldridge & Kerry,
2012). The two predetermined covariates specified for this study are:

Baseline scores on outcome measures;School decile;Time from baseline to assessment (treated as categorical data) for repeated measures analyses.

To maximise statistical efficiency, both post-intervention and follow-up measurements will be included in all regressions for a given outcome, with specific contrasts being used to isolate results at any time point. There is only one planned comparison for testing the primary hypothesis so no adjustment for multiplicity is required. Given the need to make multiple comparisons for the secondary hypotheses, False Discovery Rate control will be applied to protect against Type I errors (Benjamini & Hochberg,
1995).

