## Methods

### Trial design

This is a two-arm, pragmatic, cluster-randomised controlled trial in which schools are the unit of randomisation. The trial will employ an open-label, repeated measures, parallel and one-way crossover design. Children will be naturally clustered by school and this design will prevent contamination between trial arms (intervention and waitlist). One-way crossover will occur when children allocated to the waitlist crossover to start receiving the intervention after a set time. The trial has been approved by the New Zealand Health and Disability Ethics Committees (14/NTA/13) and is registered with the Australia/New Zealand Clinical Trials Registry (ACTRN12614000453684) http://www.anzctr.org.au/default.aspx.

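### The primary RM-ANCOVA as written has no school-level term although schools are randomised; run that way, between-arm tests exceed 5% for any positive intracluster correlation

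*Protocol article*

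**What the plan says.** Three parts of the protocol article bear on this point.

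- **Trial design.** The study is a "cluster-randomised controlled trial in which schools are the unit of randomisation". The same section says: "Children will be naturally clustered by school".
- **Sample size.** The base figure, 64 per arm under individual randomisation, is then "adjusted by a design effect of 0.98, which accounts for clustering and adjustment for baseline values". The result is "a total of 126 children from 14 schools".
- **Statistical analysis.** The model is introduced with: "A Repeated Measures Analysis of Covariance (RM-ANCOVA) analysis of the data will allow comparisons of between-subject (intervention versus waitlist control) and within-subject" factors and their interactions. The adjusters are the baseline score, school decile and categorical time, plus any covariates that the blind review adds, such as gender.

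The cluster level appears in the Descriptive statistics section and in a remark on the efficiency of individual-level over cluster-level covariates. It does not appear in the inference. The Blind review section allows a change of model before the final analysis, but does not say that school must enter it.

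**The concern.** All children in a school share one allocation, so arm varies between 14 schools and not between children within a school. The error term for the arm comparison must therefore contain between-school variation. The model as written places arm in the between-subject stratum and has nothing that carries variation between schools.

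Some correlation within schools is to be expected. School staff choose the children by their own judgement (Participants), and the programme is delivered to groups (Intervention). The fidelity maximum of 112 per cluster is 14 items × 8 sessions, which fits one group per school.

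Decile does not fill the gap. It has three levels, with target counts of 4, 6 and 4 schools, and schools within a level can still differ. The design effect in the sample size does not fill it either: it governs how many children are recruited, not how the standard error is computed.

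At stake is the 5% error rate of the single primary test and the validity of the between-arm secondary p-values. False discovery rate control cannot repair p-values that are too small when they enter the procedure.

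**Working it through.** **1. The plan's own figure.** Inputs from Sample size: difference 5 t-score points, 5% significance, 80% power. Assumed: SD 10 (not stated) and a two-sided test (sidedness is not stated, but the hypothesis is non-directional). The exact two-sample t-test needs 64 per arm (power 0.801), matching the stated starting point. Then 64 × 0.98 = 62.7, rounded up to 63 per arm and 126 in total. The stated figure reproduces. Children per school: 126/14 = 9 at the required size and 154/14 = 11 at the recruitment target.

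**2. Error rate with no school term.** For m children per school, clustering multiplies the variance of the arm contrast by

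DE = 1 + (m − 1) × ICC,

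where ICC is the within-school correlation left after adjustment. A test that omits this factor has true two-sided error

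2 × [1 − Φ(1.96/√DE)].

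Example: m = 9, ICC = 0.05 gives DE = 1 + 8 × 0.05 = 1.40, 1.96/√1.40 = 1.66, and error 9.8%.

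The formula was checked by simulation: 14 schools in strata of 4, 6 and 4, randomised within stratum, child-level ANCOVA on arm, baseline and decile at a single post-baseline time, baseline correlation 0.5, 6,000 runs per setting.

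| Assumed ICC | DE, m = 9 | Formula | Simulated | DE, m = 11 | Formula | Simulated |
|---|---|---|---|---|---|---|
| 0 | 1.00 | 5.0% | 4.8% | 1.00 | 5.0% | 5.3% |
| 0.01 | 1.08 | 5.9% | 5.7% | 1.10 | 6.2% | 6.3% |
| 0.03 | 1.24 | 7.8% | 7.4% | 1.30 | 8.6% | 8.3% |
| 0.05 | 1.40 | 9.8% | 10.1% | 1.50 | 11.0% | 10.9% |
| 0.10 | 1.80 | 14.4% | 15.5% | 2.00 | 16.6% | 16.9% |

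The simulated model includes decile, and the excess remains. On the same simulated data a school-level analysis with 10 df (14 schools less intercept, arm and two stratum terms) stays between 4.6% and 5.3%.

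**3. What the 0.98 suggests about the ICC.** The article does not say how 0.98 was built. Assume the usual product for m = 9, with r the correlation between baseline and outcome:

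(1 + 8 × ICC)(1 − r²) = 0.98.

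The clustering factor is then 0.98/(1 − r²), and the ICC is that factor less 1, divided by 8.

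| r | Clustering factor | Implied ICC | Error if school is omitted |
|---|---|---|---|
| 0.3 | 1.08 | 0.010 | 5.9% |
| 0.5 | 1.31 | 0.038 | 8.6% |
| 0.6 | 1.53 | 0.066 | 11.3% |
| 0.7 | 1.92 | 0.115 | 15.7% |

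The implied ICC is positive once r² exceeds 0.02, that is, r above about 0.14. The protocol reports at least moderate test-retest reliability for the MASC-10, so an r above that value is plausible. On this reading the planning itself assumes a positive ICC.

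**The case against.** The strongest reply is that this is a condensed article, that the full analysis plan is not shown, and that error structure is the kind of detail such a plan supplies. A random effect is not a covariate, so its absence from a covariate list does not prove that it was excluded. The authors clearly know that the data are clustered, and the blind review may choose another model.

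Part of this stands. A reader might infer that the children will be analysed as independent and that the primary test does exceed 5%. The article says neither. The first is an inference from omission. The second needs a positive ICC and a model run exactly as written, and at an ICC of zero the error stays at 5%.

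A reader might also infer that every secondary result is affected. That is too broad. In the comparison of post-intervention with follow-up within children, a school intercept largely cancels. The hypothesis relating change in knowledge to change in outcomes is not an arm contrast. Nor must the RM-ANCOVA be discarded, since it can be fitted as a mixed model with a school term.

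The reply does not remove the point. The article does not defer its model: it names the model, places arm between subjects, and lists adjusters, contrasts and multiplicity control. For this randomisation that specification is unsuitable, not merely brief. The blind review is permitted to change it but not required to, and whether the unit of randomisation enters the primary test should be settled before the data sets exist.

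**Conclusion.** The point holds in conditional form. It is certain that the model as written includes no school-level term, and that this does not match the randomisation of schools or the clustering allowance in the sample size. The size of the effect is not certain, because the ICC and the baseline correlation are not given. If the model is run as written, the true two-sided error of the between-arm tests is about 6% to 17% for an assumed ICC of 0.01 to 0.10 and 9 to 11 children per school. If 0.98 factors as assumed above, it is about 6% at r = 0.3, 8.6% at r = 0.5 and 15.7% at r = 0.7. These figures apply to the primary outcome and the between-arm secondary contrasts. They should be resolved before the final analysis because they bear on the primary test.

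**What to change.** State in the Statistical analysis section that the RM-ANCOVA will be fitted as a linear mixed model with a random intercept for school and child-level correlation for the repeated measures. Keep arm, baseline score, the three-level decile stratum and categorical time. Specify degrees of freedom suited to 14 schools, for example Kenward-Roger or between-school degrees of freedom. An equivalent school-level analysis of baseline-adjusted means, on about 10 df, would also serve. Whichever is chosen should be prespecified, not left to the blind review, and should cover all between-arm outcomes. It would help to report the ICC and baseline correlation behind the 0.98.

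The change is to wording only. SAS and R, both already named, can fit these models, and recruitment and conduct are unaffected. The price is wider confidence intervals for the arm comparison.

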**Methods/design:**

In this two-arm, pragmatic, cluster-randomised controlled trial, 154 children will be recruited from 14 schools. All mainstream schools in the region will be eligible and a convenience sample of 14 schools, stratified by decile ranking (i.e. low, medium, and high) will be recruited. Eight to twelve students aged 11–13 years from each school will be recruited by senior school personnel. Following consent, schools will be randomised to either the intervention or waitlist control arm of the trial. The study will employ a parallel and one-way waitlist-to-intervention crossover design. Each cluster’s involvement will last up to 19 or 31 weeks depending on allocation to the intervention or waitlist respectively. The primary outcome is symptoms of anxiety and secondary outcomes are symptoms of depression, self-esteem, participation in daily occupations and wellbeing. Outcome measurement will be repeated at baseline, post-intervention and again at 8–9 weeks follow-up. Planned statistical analyses will utilise repeated measures analysis of covariance. The primary analysis will be based on an intention-to-treat analysis set and include only parallel data. The crossover data will only be used in secondary analyses.

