**Total score = total number of ‘Yes’s (max 14)**	

### Waitlist-control

The waitlist group will not receive any input during the parallel component of the trial and will only complete the baseline and post-intervention outcome measures. In the crossover component of the trial, the waitlist group will go on to receive the intervention as described.

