### Outcome measures

Participants will complete all outcome measures on three or five occasions, depending on the arm of the trial to which they are allocated (Figure 
1).

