### Efficacy end points (EEP)

The primary EEP for this study will be one-week post-intervention on completion of the post-intervention primary outcome measure, the MASC-10. Secondary EEPs for this study will at the 8–9 week follow-up on completion of the primary outcome measure (MASC-10) and post-intervention and 8 week follow up completion of all other outcomes.

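### The arm-by-time model calls for follow-up contrasts, but the waitlist arm has no untreated follow-up, so any claim of sustained benefit is uncontrolled

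*Protocol article*

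**What the plan says.** The Statistical analysis section of the protocol article describes a repeated-measures ANCOVA that gives "comparisons of between-subject (intervention versus waitlist control) and within-subject (repeated measures on outcomes) factors and their interactions". Time from baseline enters as a categorical covariate. Follow-up scores enter every model, and the reason given is efficiency: "both post-intervention and follow-up measurements will be included in all regressions for a given outcome". Single time points are then to be examined separately, "with specific contrasts being used to isolate results at any time point".

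The Waitlist-control section says that during the parallel part this arm "will only complete the baseline and post-intervention outcome measures". In the crossover part "the waitlist group will go on to receive the intervention as described". The Outcome measures section agrees: "Participants will complete all outcome measures on three or five occasions, depending on the arm of the trial". So does the abstract, where each cluster's "involvement will last up to 19 or 31 weeks depending on allocation to the intervention or waitlist respectively".

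The abstract and Sets for analysis restrict the primary analysis to the parallel data. The Secondary ITT set adds what the waitlist arm contributes after crossover.

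Follow-up carries weight in the objectives. The Aim includes whether improvements last over 8–9 weeks. The second secondary hypothesis concerns change between post-intervention and follow-up. The secondary efficacy end points include the later assessment of every outcome and are reached "on completion of the primary outcome measure (MASC-10) and post-intervention and 8 week follow up completion of all other outcomes".

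**The concern.** The model and the measurement schedule do not fit together. An arm-by-time interaction with two post-baseline times needs both arms at both times. In the parallel data one of the four cells is empty by design, not through dropout, so no missing-data method can fill it from observed untreated children.

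What is at stake is mainly the follow-up conclusion. Without an untreated comparator at that time, later change in the intervention arm mixes any lasting effect with maturation, a different point in the school year, and regression to the mean in children who were nominated because they showed early symptoms. A lesser risk concerns the primary analysis: if the named method were run in its classical form, which keeps only children with every repeated measure, the waitlist arm would drop out.

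**Working it through.** **Inputs.** Primary end point 9 weeks after baseline (Primary outcome measure). Follow-up 8–9 weeks after the intervention, with a 2-week window (Minimising loss to follow-up). Involvement up to 19 or 31 weeks (abstract). Sample size: 64 per arm × design effect 0.98 = 62.7, rounded up to 63, so 126 children, as the protocol states. The protocol gives no figure for the contrasts at issue, so the check is one of estimability.

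**Step 1: which cells exist in the parallel data.**

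| Arm | Baseline | Week 9 | Follow-up |
|---|---|---|---|
| Intervention | yes | yes | yes |
| Waitlist | yes | yes | none |

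The intervention arm has 3 occasions. The waitlist arm's 5 are read as 2 in the parallel part plus 3 around its own intervention.

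**Step 2: timing.** 31 − 19 = 12, so the waitlist arm appears to start treatment at about week 12. The intervention arm's follow-up falls at about weeks 17–19 (9 + 8 = 17; end of involvement at 19). That is 17 − 12 = 5 to 19 − 12 = 7 weeks into the waitlist arm's own 8-week programme. If one of its later assessments is a repeat baseline at about week 12, that score is untreated but does not stand at the follow-up time. This timing is inferred; the empty cell in Step 1 does not depend on it.

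**Step 3: estimability.** Take E(Y) = b0 + b1·A + b2·T + b3·A·T + b4·B, with A = 1 for intervention, T = 1 for follow-up and B the baseline score. With 63 waitlist children measured once and 63 intervention children measured twice there are 63 + 126 = 189 rows. T = 1 occurs only where A = 1, so the columns T and A·T are identical and the rank is 4 of 5.

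- Arm contrast at week 9 (b1): estimable.
- Arm-by-time interaction (b3): not estimable.
- Arm contrast at follow-up (b1 + b3): not estimable.
- Change from post-intervention to follow-up within the intervention arm (b2 + b3): estimable, without a control.

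Setting b3 = 0 restores full rank, but the arm effect at follow-up is then simply b1, the 9-week effect carried forward by assumption.

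**Step 4: the efficiency reason.** With complete data, residual variance 1 and no school effect, the variance of b1 is 0.03180 to 0.03181 with the follow-up rows and 0.03181 without them, for within-child correlations of 0.3 to 0.7. The follow-up rows are absorbed by the time term and add almost nothing to the primary contrast.

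**Step 5: the Secondary ITT set.** The waitlist arm's own follow-up comes after it has had the intervention. An arm contrast there compares treated with treated. What the set can support is a pooled change from post-intervention to follow-up over both arms' treated periods.

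**The case against.** The strongest reply is that the hypotheses never ask for the contrast that cannot be estimated. The primary hypothesis and the first secondary hypothesis compare arms at post-intervention only, the second is a change over time with no arm comparison, and the end-point section lists times and measures rather than contrasts. This stands: a reader might infer that a between-arm test at follow-up is planned outright, and the text does not say so. It does not remove the problem, because the analysis section expressly specifies the interactions and contrasts at each time for every outcome, and the design cannot supply them.

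A reader might also infer that the primary analysis fails or would contain no controls. The protocol does not support that. It speaks of regressions and contrasts, treats time as a categorical covariate, names SAS and R as well as SPSS, and lets the blind review select alternative models. That fits a long-format model, in which children measured once are kept. Loss of the waitlist arm needs a complete-case procedure that the text neither states nor excludes.

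Nor does the protocol infer sustained benefit from a non-significant change; its second secondary hypothesis predicts a difference. Lack of a concurrent control after crossover is inherent in the openly described waitlist design, but the Limitations section does not mention it.

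Finally, the negligible efficiency gain was shown for complete data only. With attrition, a follow-up score could carry some information about an intervention child who missed week 9. That is fair, and it means that including those scores does no harm to the 9-week contrast in a suitable model.

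**Conclusion.** The concern holds for follow-up. In the Primary ITT set the arm-by-time interaction and the follow-up arm contrast are not estimable (rank 4 of 5, no waitlist follow-up scores), and the Secondary ITT set offers only treated against treated. The sustainability aim and the follow-up end points therefore rest on an uncontrolled change, which can be estimated but not attributed to the intervention.

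The 9-week primary contrast is sound in a long-format mixed model. It is at risk only if a classical complete-case RM-ANCOVA is used.

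The empty cell rests on the Waitlist-control section alone. The week-12 start is an inference from the stated maximum durations, as the flow figure is not shown. The direction and size of any maturation, term or regression effect cannot be derived from the protocol.

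**What to change.** Before unblinding, amend the Statistical analysis section, the Aim, the second secondary hypothesis and the end points as follows.

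- Estimate between-arm effects for all outcomes at the 9-week measurement only, with a baseline-adjusted mixed model that includes school and keeps children measured once. State that complete-case RM-ANCOVA will not be used.
- Drop the arm-by-time interaction and any between-arm contrast at follow-up, in both ITT sets.
- Report change from post-intervention to follow-up as an estimate within treated periods (the intervention arm in the Primary ITT set, both arms pooled in the Secondary ITT set), with a confidence interval and labelled uncontrolled.
- Word the sustainability aim and end points as description of later change, and add the missing follow-up control to the Limitations.

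The cost is a weaker claim at follow-up and some redrafting. No new data are needed, and the primary comparison is unchanged.
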